### **Randomization**

A stratified blocked randomization technique will be used. The subjects will be randomized to the **Experimental Group** or the **Control Group** and stratified into three groups based on their GA:

- 26-28 and 6/7 weeks gestation,
- 29-30 and 6/7 weeks gestation,
- 31-32 and 6/7 weeks gestation. (Pilot Study – Discontinued Spring 2013)

A blocked randomization technique will be used to ensure approximately equal number of subjects are in each group. The randomization will be generated by SAS v. 9.1 statistical software program. Just prior to randomization, the inclusion and exclusion criteria will be reviewed for each candidate.

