### **NTrainerRT® Therapy**

The patterned orocutaneous stimulus has been designed to mimic the temporal aspects of ororhythmic activity associated with the NNS, incorporating frequency modulation across the six-suck cycles. As shown in the plot that follows (figure 2), the synthetic NNS train is based on the results of modeling of the initial six-cycles of a NNS burst (compiled from modeling studies of N=1756 bursts among healthy preterm infants). This pattern is generated by a digitally controlled linear servo motor and pressurized actuator, which is pneumatically coupled by way of Luer tubing to the infant's preferred *Soothie*® silicone pacifier (Figure 1-a)(Figure 1-b). The synthetic orocutaneous stimulus includes frequency modulation with the following sequence of cycle periods within the burst: 510, 526, 551, 580, and 626 ms producing 275 micron deflections of the *Soothie*™ nipple cylinder with 2-second interburst *pause periods*. This configuration transforms the pacifier into *pulsating nipple*, which resembles the spatiotemporal pattern of the NNS.

[figure not shown][figure not shown]

**Figure 1-a.** NTrainer System®.

[figure not shown]

**Figure 1-b.** NTrainer System® hand piece with a silicone Soothie® pacifier.

[figure not shown]

**Figure 2.** Positive and negative pressure appearance of a *Soothie*® silicone pacifier (exaggerated for visual appreciation), and a non-nutritive suck train pattern in time.

Recent studies in preterm infants have demonstrated that NTrainer System® entrainment enhances maturation of NNS both in healthy preterm infants and in preterm infants with respiratory distress syndrome (RDS) (Barlow et al., 2008; Poore et al., 2008). The preterm infants who have received this patterned orocutaneous stimulation outperformed their control groups on quantitative measures of NNS behaviors. Furthermore, the trained infants had an accelerated transition-to-oral feeding, surpassing their control counterparts; however, the trial was not powered to study transition-to-oral feed as the primary outcome.

This study is a multicenter randomized clinical trial to evaluate the effect of NTrainer System® entrainment on transition from gavage to full oral feeds during a critical period of brain development in infants born between 26 and 32 weeks gestational age. NTrainer System® stimulation is hypothesized to facilitate oral feeding maturation, improve growth, and shorten hospital stay.

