## **STATISTICAL ANALYSIS**

### **Sample Size Calculation**

The principal study subjects are infants born between 26 and 30 weeks gestation. The sample size was calculated based on the alternative hypothesis that the preterm infants born before 31 weeks gestation in the experimental group will transition initiation of oral feeds to attaining full oral feeds 5 days earlier than

the control group. Data from Simpson et al, (2002) demonstrate that infants who underwent a standard protocol for early oral feeding advance transitioned to the full oral feeds at  $23 \pm 12$  (Mean  $\pm$  SD) days. All subjects will be followed until they attain full oral feeds. Therefore it is expected that the time to full oral feeds will be available for all or nearly all subjects (i.e. there will be little or no censoring of event times). Since the time to full oral feeds may be right skewed, the Wilcoxon Rank Sum test will be used as the primary analysis. We consider 5 days to be a clinically significant difference between the control and the experimental group. Thus, 105 infants in each group of a two-sided alpha of 0.05 yield 80% power ( $\beta=0.2$ ) to detect a 5 day difference in the time to reach full feeds.

The percent of subjects with censored times are those leaving the trial prior to attainment of full oral feeds. Censored data will be assessed in a fully blinded way when 75% of the target sample size has completed the protocol. If rate of censoring is higher than 10% at this time, the planned use of the Wilcoxon Rank sum test will no longer be considered appropriate, and a log-rank test will become the primary analysis. Since the log-rank test has lower power, the sample size will need to increase to 160 subjects per group to achieve 80% power to detect a 5-day difference in median time to full oral feeds.

The infants between 31 and 32 weeks of gestation may attain full oral feeds much sooner compared to the younger gestation; therefore the effect size may vary considerably in this group of preterm infants. We will include the 25 subjects per group born between 31 and 32 weeks gestation to obtain pilot data on their effect size in order to calculate the sample size for this group, but the primary analysis will not include these subjects.

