### **Data Monitoring and Education**

The patient will be considered to have completed the study, after attaining full, independent oral feedings for two days or after death, discharge, or transfer to a hospital not participating in the study.

Data will be collected using a case report form (Appendix C). Additional study-related documents, study references and information upgrades regarding the project will be available at this site.

If subject is transferred to another hospital following completion of the NTrainer System® intervention, we will have the ability to obtain follow-up data on outcomes.

A representative from KCBioMedix will monitor the progress of the study. The monitor will communicate with each center from the beginning and throughout the study to provide education and weekly review concerning the protocol, electronic randomization, CRF, and data forms for the trial. Monitoring will include 100% review of the primary outcome and secondary outcomes. It will be necessary for the monitor to review those portions of the patients' medical records pertinent to the study.

The monitor will complete clinical monitoring in accordance with Good Clinical Practice Guidelines (GCP).

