### **PUBLICATION POLICY**

All information is to be considered confidential. Any scientific publication regarding this study will be reviewed and agreed by all the participating parties (ie. SCVMC, CCMC, DUMC and KCBioMedix).

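### Centre enters neither the primary test, nor its log-rank fallback, nor the Cox model of this multicentre trial, which costs power if centres differ

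*Protocol*

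**What the plan says.** - **Design.** The background section on NTrainerRT Therapy states: "This study is a multicenter randomized clinical trial". The number of centres is not given. Publication Policy lists "SCVMC, CCMC, DUMC and KCBioMedix" as the participating parties; the last is the sponsor, so three centres is a reasonable inference and no more.
- **Randomisation.** Under Randomization, infants are "stratified into three groups based on their GA". The section adds: "A blocked randomization technique will be used to ensure approximately equal number of subjects are in each group". Block size is not stated, and centre is not mentioned. Data Monitoring and Education refers to "weekly review concerning the protocol, electronic randomization, CRF, and data forms for the trial" without saying whether lists are held per centre.
- **Primary analysis.** Sample Size Calculation states that "the Wilcoxon Rank Sum test will be used as the primary analysis". If blinded review shows more than 10% censoring, a log-rank test takes its place. No strata are named for either test.
- **Supportive analysis.** Data Analysis adjusts the Cox model for age group and for comorbid conditions that interrupt feeding, not for centre.
- **Sample size.** "105 infants in each group of a two-sided alpha of 0.05 yield 80% power", for a 5-day difference with SD 12 days.
- **Standardisation.** Outcome Measures and Appendix B set one feeding-advancement protocol for both arms, with criteria for starting oral feeds and for a successful feed.

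**The concern.** The endpoint counts days from the start of oral feeding to full oral feeding, and units may differ in it. Appendix B gives minimum conditions for starting oral feeds but not how soon a unit must start once they are met. Sessions may be given three or four times a day, and local breastfeeding practice is left unchanged. If centres differ in mean time to full feeds, an analysis that ignores centre counts that spread as noise.

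The trial is sized at 80% power with no evident reserve, so avoidable noise matters. The protocol itself fixes the randomisation factor, the primary test, its fallback and the Cox covariates, so this concerns a stated method rather than a detail left for later.

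**Working it through.** **1. The plan's own figure.** Inputs from Sample Size Calculation: difference 5, SD 12, two-sided alpha 0.05, power 80%.

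n per arm = 2 × (1.96 + 0.842)² × 12² / 5² ≈ 90.4, so 91. Dividing by 0.864, the minimum relative efficiency of the Wilcoxon test, gives 91 / 0.864 = 105.3, which matches 105. Power at an effective n of 105 × 0.864 is 80.1%. The protocol does not name this inflation; it is inferred because it reproduces the figure.

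**2. What centre contributes.** Assume three equal centres with means shifted by −d, 0 and +d days, and total SD 12.

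- Between-centre variance = 2d²/3.
- Share of total variance (ICC) = (2d²/3) / 144.
- Centre-driven SD of the arm difference, if allocation ignores centre = √(2 × (2d²/3) / 105).

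| d (days, assumed) | Centre variance | ICC | Centre-driven SD | 95% range |
|---|---|---|---|---|
| 0 | 0 | 0 | 0 | 0 |
| 3 | 6 | 0.04 | 0.34 | ±0.66 |
| 6 | 24 | 0.17 | 0.68 | ±1.33 |
| 8 | 42.7 | 0.30 | 0.90 | ±1.77 |

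These amounts are part of the ordinary standard error, 12 × √(2/105) = 1.66 days, not additional to it. At d = 6, removing the centre part leaves √(1.66² − 0.68²) ≈ 1.51 days.

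**3. Power by simulation.** Set-up: 210 infants, three equal centres, gamma-distributed times with control mean 23 and total SD 12, a 5-day shift, blocks within gestational age only.

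| d (days, assumed) | Plain rank-sum | Centre-stratified rank-sum |
|---|---|---|
| 0 | 90% | 90% |
| ±3 | 89% | 90% |
| ±6 | 88% | 94% |
| ±8 | 86% | 96% |

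The levels exceed 80% because of the assumed skew and the conservative inflation in step 1; the comparison across columns is what matters. With normal data (2,000 runs per setting), the plain and stratified tests gave 84.3 v 83.6% at ICC 0, 85.4 v 86.0% at 0.05, 83.0 v 86.2% at 0.10 and 82.6 v 89.2% at 0.20.

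**4. Analysis or randomisation?** In separate gamma runs (3,000 per setting, blocks of 4 assumed), the stratified test had power 91, 93 and 97% at d = 3, 6 and 8 without centre blocks, and 92, 94 and 97% with them. In the normal-data runs at ICC 0.20, the SD of the estimate was 1.65 days unadjusted, 1.49 adjusted for centre, and 1.45 with centre blocks and adjustment. Almost all the gain comes from the analysis.

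Centre blocks do even out numbers: the largest within-centre arm difference averages about 8 infants without them (95th percentile 16, of about 70) and about 1.6 with them (95th percentile 3).

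**5. Type I error.** Without centre blocks, the plain test rejected in 4.8 to 5.2% of null trials. With centre blocks and no centre in the analysis, its size fell to about 3% at d = 6.

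**The case against.** The strongest reply is that nothing here is an error. Several stronger readings are tempting and fail:

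- **That the result would be biased or the test invalid.** Chance imbalance within centres is covered by randomisation, and the simulated size stays near 5%.
- **That 105 per arm is wrong.** It reproduces. If 12 days is the total SD, centre variation is already budgeted. Only if 12 were a within-centre SD would power with the plain test fall, to about 78, 76 and 71% at ICC 0.05, 0.10 and 0.20. The protocol does not say which it is.
- **That the randomisation must be rebuilt.** Step 4 shows that new lists add about a point at most. The pilot stratum is marked as discontinued in Spring 2013, so recruitment appears to be under way, and new lists cannot help infants already randomised.
- **That local practice governs the endpoint.** Appendix B standardises advancement in both arms. The staff listed under NeoSuckRT Assessment perform assessments; the text does not say that they deliver therapy. The reference to the physician's orders follows the list of milk types, while the volume threshold is fixed at 120 ml/kg/day or more.
- **That blocks certainly run across centres.** The protocol does not say how the lists are held.

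It is also fair to say that the centre gaps are assumed. At d = 6 the fastest and slowest centres differ by 12 days, a full SD; at d = 8 by 16 days against a mean of 23. At d = 3 the gain is about a point, and at d = 0 there is none. A separate analysis plan could add centre.

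What stands is that the protocol fixes these methods, names age group as an adjustment factor in several places, and never names centre.

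**Conclusion.** The point holds as one of efficiency. A multicentre trial with an unstratified primary test gives up power wherever centres differ. The loss is nil if they do not, about 1 percentage point at shifts of ±3 days, about 6 at ±6 and about 10 at ±8. These figures rest on three equal centres, total SD 12 and assumed centre shifts; the documents give no between-centre variance, and the common feeding protocol makes the larger shifts less likely. Validity and the stated sample size are unaffected. Because the remedy is nearly free, it is worth making.

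**What to change.** In Sample Size Calculation and Data Analysis, name centre as a stratum in the primary rank-sum test (van Elteren form), in the log-rank fallback and in the supportive Cox model. Apply this to all infants in the primary population, including those already randomised. The secondary feeding times follow, since they are to be analysed in the same way as the primary outcome. Make the change before any comparison by arm is seen, and keep any separate analysis plan consistent with it.

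The cost is a few words of text and no extra infants. The downside is that nothing is gained if centres do not differ.

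Under Randomization, state whether lists are kept by centre. If they are, the stratified analysis is needed for a second reason: the plain test is then conservative. If they are not, per-centre lists for the remaining infants are optional: 3 centres × 2 active gestational-age strata = 6 lists, averaging 210 / 6 = 35 infants. They add little power, and smaller strata make allocations somewhat easier to guess unless block sizes vary.

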## NTRAINER SYSTEM® INTERVENTION

### Study Time line:

[figure not shown]

### **Infant Preparation-Positioning** (*Applicable to all assessment and stimulation/recording sessions*)

The infant will be cradled in a supportive inclined posture, swaddled, with limbs positioned at midline, and background/overhead lighting dimmed in the isolette area to promote eye contact with the tester. Infants may also be positioned for assessment and training while still remaining in their isolette as would be appropriate for their gestational age. The infant will remain connected to the usual NICU monitors at all times for observation of respiration, heartbeat and oxygen saturation by the nurse.

**Figure 3.** Preterm infant receiving NTrainer System® patterned orocutaneous stimulation

### **NeoSuckRT® Assessment**

The development of nipple compression pressure dynamics associated with the NNS will be monitored using the NeoSuckRT® program. This assessment of NNS will occur 15 minutes prior to a gavage or oral feed that is not assigned to an NTrainer System® intervention. A 3-minute digital record of NNS activity will be sampled and the digitized record of NNS behavior will be subjected to quantitative indexing of NNS amplitudes and cycle periods within burst, using a specially designed NNS waveform discrimination algorithm. After the NeoSuckRT® procedure is completed, the infant will be fed by the attending nurse. If the baby is able to feed by mouth, the investigator may observe the feeding. Speech pathology, physical/occupational therapists, research coordinators, or staff nursing may perform the assessments.

All infants enrolled in the study (**experimental group** and **control group**) will first start on the NeoSuckRT® program. They will have at least two assessments including clinical assessment by the nursing staff or research staff and assessment using the NeoSuckRT® program prior to the study intervention. The NeoSuckRT® assessment will be done at least three times a week before, during and after the study intervention is completed until the infant reaches the primary outcome.

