## STUDY PROTOCOL

### **BACKGROUND**

The development of sucking behaviors reflects neurobehavioral maturation and organization (Goldson 1987). The early components of sucking have been demonstrated to occur in fetal life from about eight weeks post-menstrual age. Oral and gag reflexes first appear at about 12 weeks, and sucking appears at 24 weeks. Sucking and swallowing are present by 28 weeks; however, they are not coordinated until about 32 to 34 weeks. The spatiotemporal stability of an infant's non-nutritive suck (NNS) reflects the emergent rhythmic structure of the developing central pattern generators (CPGs) localized to pontine and medullary centers in the infant's brainstem (Barlow & Estep 2006; Barlow 2009).

Appropriate oral experiences are critical in the final weeks of gestation when the central patterning of suck and feeding skills are being refined. Interruption of these experiences due to prematurity or medical interventions (i.e., orofacial trussing due to oxygen-ventilation therapy and feeding tubes) may impair fragile brain mapping of these critical functions (Estep et al. 2008; Stumm et al. 2008; Poore et al. 2008).

From a clinical perspective, the ability to feed depends upon a coordinated suck, swallow, and breathing pattern. Often, premature infants have delayed or uncoordinated pattern of suck-swallow-breath and poor state control (Mizuno & Ueda, 2006; Tosh, McGuire, 2006; Barlow et al., 2001; Pinelli & Symington, 2005; Cevasco & Grant, 2005; Lau & Kusnierczyk, 2001; White-Traut, et al., 2005; Stumm et al., 2008). These conditions significantly affect their abilities to sustain full oral feedings. In the interim, infants are fed by gavage tube until they are mature enough to take milk directly from the breast or bottle.

NNS via a pacifier during gavage feeding facilitates the transition from gavage to breast and bottle feeding because NNS facilitates development of sucking behavior, allowing infants to achieve coordinated oral feeding faster (Pinelli & Symington, 2005; Rocha et al., 2007).

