### **Data Analysis**

The primary outcome of the study is the time to attain full oral feeds. All subjects will be followed until they attain full oral feeds. Wilcoxon Rank Sum test will be used to test for a difference between the two groups. A secondary, supportive analysis will be performed using the log-rank test, with the understanding that this test will likely be underpowered. As mentioned in the sample size section, in the event that the rate of censoring is higher than the 10% of evaluable subjects expected, the Wilcoxon Rank Sum test will not be considered appropriate and the log-rank test will be elevated to the primary analysis method.

The null hypothesis is that there will be no difference in the median times to full oral feeds in the experimental group versus the control group, this will be tested using a 0.05 two-sided significance level, with the following hypotheses:

$$H_0 : M_{NT} = M_C$$

$$H_a : M_{NT} \neq M_C$$

Where  $M_{NT}$  and  $M_c$  refer to the population medians in the NTrainer System® group and the control group, respectively.

The time to event will be measured as the number of days from the initiation of oral feedings to full oral feeding. Kaplan-Meier survival curves will be produced to illustrate the time of attainment of full oral feeds in the two groups. As a supportive analysis, a Cox proportional hazards regression model will be used to test for a difference in the time to attain full oral feeds between the two groups, while controlling for age group (26-27, 27-28, 29-30 and 31-32 weeks post menstrual age) and the presence of co morbid conditions that interrupt the feeding schedule.

Exploratory subgroup analyses of the primary outcome in each of the different gestational age groups (26-27, 27-28, 29-30 and 31-32 weeks post menstrual age) will be performed to evaluate for any difference in

the effect of the NTraining® at different gestational ages, and within groups having and not having co morbid conditions that interrupt the feeding schedule.

The secondary outcome variables of time from the initiation of the NTrainer System® training to first and fourth successful oral feeds will analyzed in the same manner as the primary outcome variable.

The rate of milk transfer at the time of full oral feeds will be compared between groups using an independent t-test. We will also compare the NNS parameters after the completion of NTrainer System® and at the time of full oral feeds using *t* tests.

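### The primary test of time to full oral feeds uses neither the planned baseline suck recording nor the gestational-age strata, leaving possible precision unused

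*Protocol*

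**What the plan says.** **Baseline data.** Protocol, NeoSuckRT® Assessment, covers both arms. Each infant is to have two or more assessments before training starts, and these count a clinical one as well as "assessment using the NeoSuckRT® program prior to the study intervention". On how often the device assessment is repeated, the section adds: "The NeoSuckRT® assessment will be done at least three times a week before, during and after the study intervention is completed". No minimum length is set for the period before the intervention.

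**Strata.** Under Randomization, allocation is stratified by gestational age: 26 to 28 6/7, 29 to 30 6/7 and 31 to 32 6/7 weeks. The last stratum is a discontinued pilot, and Sample Size Calculation keeps it out of the primary analysis.

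**Primary analysis.** Data Analysis states: "Wilcoxon Rank Sum test will be used to test for a difference between the two groups". If censoring exceeds 10%, "the log-rank test will be elevated to the primary analysis method". No covariate or stratification is stated for either test.

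**Supportive analysis.** The Cox model compares the arms "while controlling for age group (26-27, 27-28, 29-30 and 31-32 weeks post menstrual age", and for "the presence of co morbid conditions that interrupt the feeding schedule". Its age bands are not the randomisation strata. Suck parameters are analysed only as secondary outcomes, after training and at full oral feeds.

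**The concern.** The trial rests on the idea that more mature non-nutritive sucking leads to earlier oral feeding. If that is right, infants who suck better before training may reach full feeds sooner in either arm. Gestational age plausibly works in the same direction, and the protocol itself expects the 31 to 32 week infants to reach full feeds much sooner.

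An unadjusted test leaves this variation in the noise of the primary comparison and does nothing about a chance imbalance in baseline suck. Adjusting for a pre-treatment covariate keeps the type I error and, if the covariate is prognostic, raises power at the same sample size. What is at stake is power, not validity. The point is within a protocol review because the protocol itself fixes the primary test, the fallback and the Cox covariates.

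**Working it through.** **Inputs from Sample Size Calculation:** difference 5 days, SD 12 days, two-sided alpha 0.05, power 80%, 105 per group, Wilcoxon test, little or no censoring expected.

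**Input not in the documents:** the correlation r between a baseline suck measure and time to full feeds. A range of 0 to 0.5 is assumed.

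**1. Reproduce the plan's figure.**
- Two-sample comparison of means: n = 2 × [12 × (1.960 + 0.842) / 5]² = 90.42 per group.
- Divide by 0.864, the minimum asymptotic relative efficiency of the Wilcoxon test: 90.42 / 0.864 = 104.7, so 105. The stated figure is reproduced.
- With the normal-theory efficiency of 0.955 the same step gives 95. At 105 per group, power is then 83.9%, against 80.1% with 0.864.

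**2. Effect of adjustment, by formula.** Adjustment multiplies the residual variance by (1 − r²).
- Required n = 105 × (1 − r²), rounded up.
- Power at 105 per group = Φ(5 / [12 × √(1 − r²) × √(2 / (105 × 0.864))] − 1.96).

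| Assumed r | n per group for 80% power | Power at 105 per group |
|---|---|---|
| 0 | 105 | 80.1% |
| 0.1 | 104 | 80.5% |
| 0.2 | 101 | 81.7% |
| 0.3 | 96 | 83.7% |
| 0.4 | 89 | 86.5% |
| 0.5 | 79 | 90.0% |

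**3. Check by simulation.** Normal times, SD 12, shift 5 days, 105 per arm, 5,000 replicates per cell; Wilcoxon against a Quade-type rank analysis of covariance.

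| Assumed r | Wilcoxon | Adjusted | Gain (points) |
|---|---|---|---|
| 0 | 82.6% | 82.5% | −0.1 |
| 0.2 | 83.2% | 84.4% | 1.2 |
| 0.3 | 83.1% | 85.9% | 2.8 |
| 0.4 | 84.5% | 89.1% | 4.6 |
| 0.5 | 83.1% | 91.7% | 8.6 |

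Null rejection of the adjusted test was 4.9% to 5.1%. The Wilcoxon column should be constant; its spread is simulation error (standard error about √(0.83 × 0.17 / 5,000) = 0.5 points).

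Right-skewed (gamma) times with a scale effect gave 89.2% rising to 91.8% at r = 0.3, and to 95.2% at r = 0.5.

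**4. With strata.** A simulation with two gestational-age strata, closer to the test proposed below, gave type I error of about 5%, a loss of under 1 point at r = 0, and gains of about 1, 3 and 8 to 9 points at r = 0.2, 0.3 and 0.5.

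**The case against.** The strongest reply is that nothing here is wrong. An unadjusted Wilcoxon test is valid in a randomised trial, and 105 per group was derived for that test, so the planned power does not rely on adjustment. This stands, and it limits the point to an efficiency improvement.

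A reader might also infer three stronger things that the documents do not support.

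- **That every infant has at least two baseline NeoSuckRT recordings.** The required two assessments include a clinical one, so one clinical and one NeoSuckRT assessment would satisfy the sentence. The three-a-week schedule makes more recordings likely, but with no minimum lead-in only one is guaranteed.
- **That baseline suck is documented as prognostic.** Background says "NNS facilitates development of sucking behavior, allowing infants to achieve coordinated oral feeding faster", but that sentence is about pacifier sucking as an intervention during gavage feeding. The earlier device studies, described under NTrainerRT® Therapy, likewise report treatment effects. Neither gives a correlation between a baseline measurement and the outcome. There are reasons to expect a modest one. Training can start at 30 weeks postmenstrual age, while Background places coordinated suck and swallow at about 32 to 34 weeks. The outcome clock starts at the first oral feeding, which has its own entry criteria. If half the infants had a baseline suck value of zero (an assumption), the gain at r = 0.3 would fall to about 2 points.
- **That the change is free.** This is true of data collection only. A Wilcoxon test takes no covariate, so the named primary test and its fallback would both change, and one of six suck parameters would have to be chosen without evidence on which is most prognostic.

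Gestational age is at least as natural a candidate, since it is known for every infant and needs no imputation. That is a reason to include the strata in the fix, not to leave baseline suck out. The correlation that then matters is the one remaining within strata.

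**Conclusion.** The point holds as unused precision. A pre-intervention suck assessment is planned for every infant and gestational age is a randomisation stratum, yet neither the primary test nor its fallback uses them, and the Cox model omits baseline suck.

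The likely benefit runs from essentially nothing to 8 to 9 power points at 105 per group, over assumed correlations of 0 to 0.5. At 0.2 or below it is under 2 points, and it becomes material only from about 0.3 to 0.4. The documents do not show where in this range the trial lies. The case for changing rests on asymmetry: under 1 point is lost if the covariate is useless, and type I error stays near 5%. The point does not show that the trial is underpowered or that its planned test would mislead.

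**What to change.** Before unblinding, amend Data Analysis as follows.

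- **Primary test:** a rank-based analysis of covariance of time to full oral feeds. Rank the times, take residuals on the ranked covariate, and compare arms within the two randomised strata of the primary population (26 to 28 6/7 and 29 to 30 6/7 weeks).
- **Covariate:** one named NeoSuckRT parameter, averaged over whatever records precede the first session. NNS Events/Minute is a reasonable choice because it is zero, not undefined, when no suck is recorded. An infant without a usable record gets the overall mean.
- **Fallback:** if censoring triggers the switch, a gestational-age-stratified, covariate-adjusted score test in place of the plain log-rank test.
- **Cox model:** add the same covariate.
- **Sensitivity analysis:** the plain Wilcoxon test as now written.

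The cost is a change to the named primary test and its fallback, with the suck parameter and the missing-record rule fixed in advance. No extra assessments or infants are needed, and 105 per group can stay because it does not depend on the adjustment.
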